This study will be a national multicenter RCT embedded within the Dutch Obstetric Consortium, in 16 centers (university hospitals, teaching and non-teaching hospitals) in cooperation with midwifery practices . Pregnant women will be randomized to RPCA or EA, before active labor has started and thereby will be informed on the assigned method of pain relief before labor starts (as in usual care). They will be only given pain relief during labor at their request or if a medical reason should arise.

Feasibility and compliance:

An ongoing study "Differences in maternal temperature and saturation after administration of remifentanil patient controlled analgesia (RCPA) or epidural analgesia (EA) during labor; STER study" in the Leiden University Medical Centre and in a recently published study on pain relief showed that randomization of women for the proposed methods of pain relief is feasible (22).

In the Netherlands, pain relief during labor is at present of major interest and an important topic for pregnant women, health care providers and politicians, as is pointed out in a recent publication of the multidisciplinary board on issues in obstetric management installed by the Dutch government. One of their advices is all Dutch women in labor should have access to

adequate pain relief during labor (23). Furthermore, the number of referrals to the hospital because of prolonged labor and request for pain relief in increasing, which will result in more women with a need of pain relief during labor. These developments will stimulate women to participate in studies on pain relief in labor.

We estimate that for proposed study for the inclusion of 1136 women in 27 months, at least 10 hospitals are needed. The collaborating hospitals have already 24 hours availability of epidural analgesia.

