## Randomisation, blinding and treatment allocation

Randomization stratified for centre and parity will take place after informed consent. Randomization will be performed through a web-based database located in the central data collection unit in the AMC in Amsterdam. Women will be randomly allocated to receive epidural analgesia of remifentanil PCA when they request pain relief during labor. There will be no blinding, as this is not possible with these two treatment methods.

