## Study procedures

Women will be asked to participate in this study before active labor has started, preferably during antenatal consult in the third trimester. They will be randomized and allocated to one of the treatment groups. If they request pain relief during labor they will be treated according to randomization with:

1. Remifentanil patient controlled analgesia; 30 microgram boluses, lockout time 3 minutes, maximum dose limit 1200 microgram/hour. Possibility of increasing or decreasing the bolus dose. When indicated EA is available.

2. Epidural analgesia; according to local protocol. When indicated RPCA is available.

There will be no additional invasive tests performed. Maternal vital parameters (temperature, heart rate, blood pressure, respiratory rate and pulse oxymetry) will be monitored non invasively at regular intervals. In the first hour after starting pain relief these parameters will be monitored with intervals of no longer than 15 minutes, after that with intervals of no longer than 1 hour. Maternal pulse oxymetry will also be monitored continuously.

Fetal heart rate and uterine activity will be measured continuously by external monitoring. When data are difficult to interpret or complications (such as meconium stained amniotic fluid, failure to progress in labor) occur, invasive monitoring by means of scalp electrode and intra-uterine pressure recording can be instituted.

Observations for known side effects will be made; respiratory depression, hypotension, nausea/vomiting and itching. Side effects will be managed by established local protocols.

Hypotension (systolic blood pressure < 90 mmHg or > 25% below baseline) will be treated with intravenous fluids, ephedrine 5 mg i.v. or phenylephrine 0.1 mg i.v. When oxygen saturation drops below 92% oxygen will be given.

Maternal pain score and pain appreciation score will be assessed using a visual analogue scale (VAS) ranging from 0-10. Women will be asked to mark the level of pain experienced during a contraction every hour starting at admission in the delivery room. Pain appreciation scores will be asked every hour, participating women will be asked to mark their level of satisfaction with analgesia. This will also be assessed using the visual analogue scale ranging from 0-10. After delivery an overall satisfaction score with pain(0-10) will be asked. Patient satisfaction will also be assessed by HADS and WDQ.

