centre and parity. First, the epidural and remifentanil group will be compared. Relative risks and 95% confidence intervals will be calculated for the relevant outcome measures. Categorical variables will be tested with the Chi-square test or Fisher’s exact test. Continuous variables will be tested with the Mann-Whitney U test. Time to delivery will be assessed using Kaplan-Meier analysis. Pain scores will be analyzed separately. We will report on pain during labor (area under the curve and mean pain score), worst pain during labor, pain scores at request pain relief. The analysis will be repeated on a par protocol basis. Subsequently, planned subgroup analysis will be done for nulliparous versus parous women, previous caesarean section, preterm labor (32 to 34 weeks and 34-37 weeks) and term labor (37-42 weeks), spontaneous versus induced labor, maternal educational level, maternal age (under 35 years versus over 35 years), multiple pregnancy. We will then use decision analysis to evaluate which intervention strategy, ie epidural analgesia or remifentanil is preferred in women who need analgesia during labor.

The low risk women will be included and analyzed in a separate trial. In the Dutch system with midwifery care and home births, there might be a difference in expectation of women with regard to pain during labor.

To be able to convince both primary and secondary care providers, these groups will be analyzed separately.

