## Recruitment and consent

Patients will be informed about the study at antenatal visits, preferably in the first trimester. They may be informed by a doctor or a nurse. They will receive the patient information and an informed consent form. During their next visit they will be asked if they want to participate in the study. Signing of the informed consent form and randomization can be done on this visit. If patients require additional information a meeting with one of the research nurses can be arranged.

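### Onset of labour and, less so, gestation at labour are usually settled after open allocation, so comparing the arms within these subgroups is not protected by randomisation

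*Protocol*

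**What the plan says.** Protocol section 8.1 puts the subgroup analyses after the intention-to-treat and per-protocol comparisons: "Subsequently, planned subgroup analysis will be done for nulliparous versus parous women". The same sentence goes on to previous caesarean section, "preterm labor (32 to 34 weeks and 34-37 weeks) and term labor (37-42 weeks), spontaneous versus induced labor", educational level, maternal age and multiple pregnancy. It does not separate factors known at randomisation from factors that become known later.

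On timing, section 6.3 has women approached "before active labor has started, preferably during antenatal consult in the third trimester". Section 9.2 allows an earlier start: information preferably in the first trimester and, at the next visit, "Signing of the informed consent form and randomization can be done on this visit". Section 1 says that women "will be informed on the assigned method of pain relief before labor starts". Section 6.2 stratifies by centre and parity only and states: "There will be no blinding, as this is not possible with these two treatment methods".

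**The concern.** A subgroup comparison carries the protection of randomisation only if membership is fixed before allocation or cannot be influenced by it. Parity, previous caesarean section, age, education and multiple pregnancy meet that test. Onset of labour usually does not. Induction is a decision, and here it will often be taken weeks or months after the woman has been told which analgesia she will receive, with neither her nor her carers blinded.

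If that knowledge changes some of these decisions, the induced women in one arm differ in kind from those in the other, and so do the women in spontaneous labour. The subgroup effect then mixes selection with the effect of the analgesia. The outcome is a self-reported satisfaction score (section 6.1.1), so differences in expectation or temperament among the shifted women could carry straight into it. A distortion could hide a real difference or create one. The stake is that a reader takes such a subgroup result for randomised evidence, because it stands in one list with results that are.

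**Working it through.** **1. The plan's own figures.** Section 4.4 gives a margin of 10% of a 10-point scale (1.0 point), SD 2.2, two-sided alpha 0.05 and 90% power.

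- Per group: 2 × [(1.960 + 1.282) × 2.2 / 1.0]² = 101.7, so 102.
- Cross-over and non-compliance of 10% and 30%: 102 / (1 − 0.10 − 0.30)² = 102 / 0.36 = 283.3, so 284 per arm and 568 in total.
- Half of the women needing pain relief: 568 / 0.5 = 1136.

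All three figures reproduce, and this point disputes none of them. They supply the yardstick of 1.0 point.

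**2. Order of events.**

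- Allocation takes place antenatally, in the third trimester by section 6.3 and possibly earlier by section 9.2.
- The woman is told her method before labour (section 1), without blinding (section 6.2).
- Gestation at labour is settled afterwards. Section 4.3 treats it that way itself, since labour outside 32 to 42 weeks is a reason for withdrawal arising after randomisation.
- Onset of labour (spontaneous or induced) is also settled afterwards. The exception is a woman whose induction had already been decided when she was randomised, and the documents do not say how many such women there would be.
- Analgesia is given only later, on request or for a medical reason during labour. The drugs themselves therefore cannot affect onset or gestation. Only knowledge of the allocation can.

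**3. Possible size of the bias.** The documents give no induction rate, no shift and no outcome difference, so all three inputs are assumptions:

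- p = induction rate in one arm, 20% or 30%
- d = rise in that rate in the other arm through knowledge of the allocation: 0, 2, 5 or 10 percentage points
- Δ = difference in pain appreciation between the shifted women and the others in the subgroup: 0.5, 1 or 2 points

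With no true treatment difference:

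- Bias among induced women = d / (p + d) × Δ
- Bias among women in spontaneous labour (absolute size) = d / (1 − p) × Δ

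Induced subgroup, in points:

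| d | smallest (p = 30%, Δ = 0.5) | largest (p = 20%, Δ = 2) |
|---|---|---|
| 0 | 0 | 0 |
| 2 | 0.02/0.32 × 0.5 = 0.03 | 0.02/0.22 × 2 = 0.18 |
| 5 | 0.05/0.35 × 0.5 = 0.07 | 0.05/0.25 × 2 = 0.40 |
| 10 | 0.10/0.40 × 0.5 = 0.125 | 0.10/0.30 × 2 = 0.67 |

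In the spontaneous subgroup the range is 0 to 0.10/0.70 × 2 = 0.29 points. No figure was worked out for the gestation subgroups, because the documents offer nothing on which to base one.

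**The case against.** There is a good deal to say for the plan as written.

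- Neither treatment has begun when labour starts, so these variables precede treatment. Each method also stays available to the other arm when indicated (section 6.3), which weakens any motive to induce differently. The documents show no evidence of a shift. This stands: bias is possible, not demonstrated.
- A reader might infer that the plan has no check on whether induction differs by arm. The text does not support that. Section 8.1 lists start of labour and gestational age among the variables to be described, and says that the two groups are compared before the subgroups are examined. By-arm frequencies are plausibly covered. What is missing is any link from them to how the subgroup results are read.
- The gestation subgroups are a weaker case. Spontaneous preterm labour is hard to shift by knowledge of an analgesia method, and the route would run mainly through the timing of induction. This also stands.
- The upper end of the illustration needs a rise of 10 percentage points in induction from knowledge of the arm alone, in women differing by 2 points, about 0.9 of the planned SD (2/2.2 = 0.91). That is an extreme corner.
- Equivalence, margin and power are set for the overall comparison. No equivalence claim is attached to any subgroup, and labelling subgroup results could be left to a statistical analysis plan.

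The last argument does not dispose of the point. The protocol itself names these comparisons as planned and places them with baseline factors, so the choice is already made there.

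**Conclusion.** The point holds in a limited form. The comparison of EA with RPCA within induced and spontaneous labour is not protected by randomisation, and the same applies, with less force, within preterm and term labour. The effect in these subgroups can be biased if knowing the allocation changes who is induced or when.

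Under the stated assumptions the bias among induced women runs from zero to about 0.67 points against a margin of 1 point. For a small shift of 2 percentage points it is 0.03 to 0.18. If allocation has no influence on onset or timing, the bias is zero and the arms within the subgroups remain comparable.

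Two stronger conclusions are tempting and go too far. One is that the arms in these subgroups have ceased to be randomised groups, or that their results are biased: the documents establish a loss of protection, not a distortion. The other is that the trial's equivalence finding is at risk: the primary intention-to-treat comparison and the sample size do not depend on these subgroups.

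**What to change.** In section 8.1:

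- Limit subgroup treatment comparisons to factors fixed at randomisation: parity, previous caesarean section, maternal age, education and multiple pregnancy.
- Report results by onset of labour and by gestation at labour as descriptive, and say that they rest on variables settled after randomisation.
- Show them next to the induction rate and gestational age at labour in each arm. Both variables are already on the section 8.1 list, so no new data are needed.

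The cost is a few lines of wording. Two planned subgroup comparisons become descriptive. Sample size, trial procedures and clinical care stay as they are.

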**Economic analysis:**

The costs consist of costs of delivery/childbirth (course and mode of delivery), postnatal maternal care (hospitalization, outpatient visits), neonatal care (admission to NICU/neonatology ward, outpatient visits) and primary care (midwife, general practitioner, maternity care).

Costs of delivery/childbirth are estimated by a detailed cost price analysis in which units of resource use (time of hospital staff, materials, equipment) are valued using cost per unit estimates comprising "true economic" costs, i.e. including shares of fixed costs and hospital overheads. Costs per units are estimated for both a teaching and a non-teaching hospital. A secondary analysis based on reimbursement fees will be performed. Other resource use (hospital days, outpatient visits and primary care) will be valued using standard prices (25).

In economic evaluations the preferred outcome measure for effectiveness is the quality adjusted life year. In obstetrics, the use of quality of life years as outcome measure might be less appropriate due to the relatively short duration of the delivery. As a result, many (cost) effectiveness studies focus on specific aspects of the delivery, such as pain relief and patient satisfaction (present proposal). These indicators are typically considered separately, but may be conflicting. In a HTA study additional to the present proposal (Development and validation of a delivery outcome measure. Principal investigator dr. [name], aanvraagnummer Projectnet 24349) a delivery-specific classification system consisting of several relevant but separate domains will be developed. The domain scores will be converted into a utility based, composite numerical index.

## Interim analysis

No interim analysis will be performed. Because of the suggested design of the trial where equivalence is expected all 1136 women have to be randomized in order to achieve sufficient power. Both remifentanil PCA and epidural analgesia are widely used in the Netherlands as pain relief during labour and no adverse events have been recorded to date.

Serious Adverse Events (SAEs) and Suspected Unexpected Serious Adverse Reactions (SUSARs) will be reported to a Data Safety Monitoring Committee (DSMC). The DSMC can order to perform an interim analysis and, if indicated, terminate the trial prematurely.

# ETHICAL CONSIDERATIONS

## Regulation statement

This study will be conducted according to the principles of the Declaration of Helsinki (version 2008) and in accordance with the Medical Research Involving Human Subjects Act (WMO).

## Recruitment and consent

Patients will be informed about the study at antenatal visits, preferably in the first trimester. They may be informed by a doctor or a nurse. They will receive the patient information and an informed consent form. During their next visit they will be asked if they want to participate in the study. Signing of the informed consent form and randomization can be done on this visit. If patients require additional information a meeting with one of the research nurses can be arranged.

## Benefits and risks assessment, group relatedness

In this study two already widely used methods of pain relief during labor will be compared. Patients who do not wish to be in the study will receive pain relief according to local hospital protocol.

Already documented risk of remifentanil PCA are maternal respiratory depression, nausea/vomiting and itching. Known risks of epidural analgesia are hypotension, increased use of oxytocin and increased risk of instrumental delivery. Maternal side effects will be part of the study outcome.

Proposed study considering cost effectiveness of RPCA as first choice versus EA could strongly improve the care for 180.000 women, giving birth in the Netherlands yearly by giving them access to pain relief during labor if needed, 24 hours a day.

## Compensation for injury

Because in this study two common methods of analgesia during labor that are already widely used will be compared, it is possible that insurance for subjects participating might not be necessary. We would like to request the possibility not to have such insurance.

The Leiden university medical centre (LUMC) has an insurance which is in accordance with the legal requirements in the Netherlands (Article 7 WMO and the Measure regarding Compulsory Insurance for Clinical Research in Humans of 23th June 2003). This insurance provides cover for damage to research subjects through injury or death caused by the study.

1. € 450.000,-- (i.e. four hundred and fifty thousand Euro) for death or injury for each subject who participates in the Research;
2. € 3.500.000,-- (i.e. three million five hundred thousand Euro) for death or injury for all subjects who participate in the Research;
3. € 5.000.000,-- (i.e. five million Euro) for the total damage incurred by the organisation for all damage disclosed by scientific research for the Sponsor as ‘verrichter’ in the meaning of said Act in each year of insurance coverage.

The insurance applies to the damage that becomes apparent during the study or within 4 years after the end of the study.

# ADMINISTRATIVE ASPECTS AND PUBLICATION

## Handling and storage of data and documents

Data will be collected using a website dedicated to studies in the Dutch consortium for obstetric studies. Data monitoring will be done by research nurses in each of the participating centers. A substantial part of these research nurses is already working for the abovementioned consortium.

Patients will all receive a trial number at randomization, Data handling will be done anonymously, with the patient code only available to the local investigator. All data will be stored in a secured database on a secured computer, to which only the investigators will have access.

## Amendments

Amendments are changes made to the research after a favorable opinion by the accredited METC has been given. All amendments will be notified to the METC that gave a favorable opinion.

## Annual progress report

The sponsor/investigator will submit a summary of the progress of the trial to the accredited METC once a year. Information will be provided on the date of inclusion of the first subject, numbers of subjects included and numbers of subjects that have completed the trial, serious adverse events/ serious adverse reactions, other problems, and amendments.

## End of study report

The sponsor will notify the accredited METC and the competent authority of the end of the study within a period of 90 days. The end of the study is defined as the last patient’s last visit.

In case the study is ended prematurely, the sponsor will notify the accredited METC and the competent authority within 15 days, including the reasons for the premature termination.
Within one year after the end of the study, the investigator/sponsor will submit a final study report with the results of the study, including any publications/abstracts of the study, to the accredited METC and the Competent Authority.

## Public disclosure and publication policy

The results of the study will be submitted for publication in national and international peer reviewed medical journals. The results will be presented at national and international congresses of the obstetricians, anesthetists and midwives. Full confidentiality is granted to all study participants, as only completely anonymized data will be presented.

No major obstacles are to be foreseen in implementation as the outcome of the proposed study will lead to more specific recommendations on the policy in women with request for pain relief during labor.

The Dutch Society for Obstetrics and Gynecology (NVOG), the Dutch Society of Anesthetists (NVA) and the Dutch Society of Midwives (KNOV) will be committed to the outcomes of the study. The results of the project will be incorporated in the guidelines of the NVOG, NVA and KNOV.

The study will be performed in ten centers that are already collaborating in a consortium (http://www.studies-obsgyn.nl/index.asp). This will not only stimulate recruitment of patients, but it also implicates that all perinatal centers will be familiar with the study protocol and its result at the end of the study. This is likely to facilitate implementation of the study results, not only in the participating centers, but also in their affiliated clinics.

The Dutch Obstetric Consortium is launching a web based platform for the public to transfer the outcomes of their studies to pregnant women. Our study results can be spread along with the results of the other studies.

